### Study design

The clinical study of the TINSA is a pragmatic pre−/post four-phase mixed methods study with non-randomised comparative groups, a convergent parallel design, and longitudinal follow-up at 3-months after hospital admission. The main quantitative element of the study incorporates descriptive and cross-sectional analytic components and measures designed to evaluate and compare four periods of time during which existing and new transdisciplinary stroke assessments are evaluated (see Fig. 1). Only the allied health stroke assessment component of the patient admission to the MHB ASU will be evaluated, and subsequent allied health input will continue as per usual care. Phase 1 (baseline, usual care) and Phase 2 (implementation of TINSA) will recruit participants experiencing symptoms of mild stroke or Transient Ischaemic Attack (TIA) and evaluate usual assessment compared to the novel TINSA (respectively). Between Phases 1 and 2, a 1-month transition phase will take place to allow staff to become familiar with the novel TINSA, complete competency training, and practice the new clinical process. Phase 3 (baseline, usual care) and Phase 4 (implementation of TINSA) will recruit participants experiencing moderate to severe stroke symptoms to evaluate usual assessment compared to the novel TINSA (respectively). Phases 3 and 4 will occur in parallel with Phase 2 and be time-limited (3 months/phase) due to time constraints on the ASU. Due to the nature of the clinical processes and staffing on the MHB ASU, neither randomisation nor blinding are feasible.

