### Outcome measures

A complete list of outcome measures is provided in Table 1.

**Table 1 Tab1:** List of outcome measures

Outcome	Measures
Time-efficiency	• Total time of allied health stroke assessments • Time from admission to enactment of social work referral • Time from admission to commencement of allied health intervention/rehabilitation • Occasions of face-to-face service with AHPs (occupational therapy, physiotherapy, speech pathology, social work) • Number of referrals to AHPs (occupational therapy, physiotherapy, speech pathology, social work) where no intervention or further assessment is indicated • Number of patients who received allied health assessment but had a negative stroke diagnosis on MRI • Time from admission to discharge from allied health (occupational therapy, physiotherapy, speech pathology) • Length of hospital stay
Cost savings	• Economic evaluation to determine difference in utilisation of hospital resources, such as bed space and AHP time
Quality of care (patient safety)	• Total number of adverse events during the hospital admission that may be related to allied health input (falls, extension of stroke, aspiration pneumonia, pressure injuries) • Missed allied health referrals (other than those due to a change in condition) • Failed discharge, defined as unplanned readmission within 30 days not related to a new episode of care
Quality of care (compliance to national stroke guidelines)	• Time from admission to allied health assessment (occupational therapy, physiotherapy, speech pathology) • Time from admission to commencement of allied health intervention (occupational therapy, physiotherapy, speech pathology) • Time from admission to mobility assessment • Time from admission to communication assessment
Utility of the novel TINSA	• Number of sections attempted/completed on the novel TINSA • Number of “stop and refer” prompts used on the novel TINSA • Number of allied health referrals identified from the novel TINSA
Patient and staff satisfaction	• Patient satisfaction survey • Staff satisfaction survey • Staff focus group
Staff trust and confidence	• Staff interprofessional trust surveys • Staff confidence surveys (pre/post competency training) • Staff building confidence surveys (monthly intervals)

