### Statistical analysis

#### Statistical power

The power calculation demonstrates the required participant number per phase to sufficiently power the study to find a minimal clinically important difference in the primary aim. The following time estimates represent the expert opinions of the AHPs working on the MHB ASU. The variation in time taken to complete discipline-specific occupational therapy, physiotherapy and speech pathology initial stroke assessment may range from 80 to 210 minutes total. The smallest clinically important improvement in time taken to allied health stroke assessment would be a decrease of 20 minutes in average total assessment time (i.e., enough time to complete another occasion of service or clinical task). Assuming a similar distribution of patients in each assessment group, a significance level of 0.05, 80% power and a standard deviation of 25 minutes, 26 patients per group will be required to detect a 20-minute difference in total assessment time.

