#### Quantitative data analysis

For each participant group, two periods of time to measure standard discipline-specific allied health assessment and the TINSA assessment will be evaluated and compared. Patient characteristics, outcomes and quantitative survey responses will be summarised for each assessment group using frequency and percent for categorical variables, means and standard deviations for approximately normally distributed continuous variables, and medians and interquartile ranges for non-normally distributed continuous variables. Differences between assessment groups will be estimated using the general linear model for continuous outcomes and logistic regression for categorical outcomes. Balance of potential confounders between the assessment groups will be investigated and multivariable adjustment will be employed where there is an apparent confounding effect. Results will be presented as differences (continuous outcomes) and odds ratios (categorical outcomes) with 95% confidence intervals. All analyses will be performed using Stata 15.1 (Stata Corp, College Station, TX) and a *p*-value < 0.05 will be considered statistically significant throughout all inferential analysis.

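### Ordinary logistic regression with odds ratios is a poor choice for uncommon yes/no safety outcomes at about 26 patients per phase, because a zero cell leaves no finite estimate or usable interval

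*Protocol article*

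**What the plan says.** The Quantitative data analysis section assigns the general linear model to continuous outcomes and logistic regression to categorical ones, and fixes the reporting: "Results will be presented as differences (continuous outcomes) and odds ratios (categorical outcomes) with 95% confidence intervals". It makes no exception for rare events. The same section plans frequencies and percents per assessment group, and multivariable adjustment where confounding is apparent.

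The comparison is made within each severity group: "For each participant group, two periods of time to measure standard discipline-specific allied health assessment and the TINSA assessment will be evaluated and compared". The Statistical power section says "The power calculation demonstrates the required participant number per phase" and arrives at "26 patients per group will be required to detect a 20-minute difference in total assessment time". No safety outcome enters that calculation.

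Table 1 lists three patient-safety measures:
- a total number of adverse events, pooling falls, extension of stroke, aspiration pneumonia and pressure injuries;
- missed allied health referrals;
- "Failed discharge, defined as unplanned readmission within 30 days not related to a new episode of care".

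Only the third is plainly a yes/no outcome per patient. Patient safety is a secondary aim, but the study hypothesis requires that quality of care is not reduced, and the abstract says non-inferiority in patient safety will be explored.

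**The concern.** A logistic regression on phase needs at least one event and one non-event in each phase. If a phase has no event, the maximum-likelihood log odds ratio runs off to plus or minus infinity and its standard error grows without limit. Adding covariates, as the section foresees, can only make separation more likely. With 26 patients per phase and an uncommon outcome, this is a realistic result.

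What is at stake is the interval. A statement about non-inferiority, even an exploratory one, rests on a confidence interval for the difference between phases. Two telling patterns are no event at baseline with several under TINSA, and no event in either phase. In both, ordinary logistic regression supplies no such interval. The team would then have to choose another method after seeing the zeros, or report percentages alone.

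**Working it through.** **Inputs from the protocol article.** 26 per phase; "a significance level of 0.05, 80% power and a standard deviation of 25 minutes"; the target is "a decrease of 20 minutes in average total assessment time". Event rates are not given, so the risks below are assumptions shown as a range.

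**The plan's own figure.** Normal approximation, two-sided: n = 2 × (1.96 + 0.84)² × 25² / 20² = 24.5, so 25 per group. The two-sample t-test gives 25.5, rounded up to 26, with 80.7% power. The stated 26 reproduces.

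**Chance of a zero cell, one yes/no outcome, equal risk r in both phases.** One phase without events: q = (1 − r)^26. At least one of the two: 1 − (1 − q)². Both: q².

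| r | q | at least one phase with none | both with none |
|---|---|---|---|
| 1% | 0.770 | 94.7% | 59.3% |
| 2% | 0.591 | 83.3% | 35.0% |
| 5% | 0.264 | 45.8% | 6.9% |
| 10% | 0.065 | 12.5% | 0.4% |
| 15% | 0.015 | 2.9% | under 0.1% |
| 20% | 0.003 | 0.6% | under 0.1% |

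The middle probability equals 50% when q = 1 − √0.5 = 0.293, that is r = 1 − 0.293^(1/26) = 4.6%.

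**Unequal risk, 5% at baseline and 10% under TINSA.** With q₁ = 0.95^26 = 0.264 and q₂ = 0.90^26 = 0.065, at least one zero cell has probability 1 − (1 − q₁)(1 − q₂) = 31.1%. A zero baseline with at least one TINSA event has probability q₁(1 − q₂) = 24.6%.

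**What the fit does.** An ordinary logit fitted to 2/26 baseline v 0/26 TINSA gave a slope of −8.7, then −18.9, then −29.3 as iterations were added. Its standard error rose from 53 to over 1.5 million. There is no finite estimate and no usable Wald interval.

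**What other methods give.**
- 2/26 baseline v 0/26 TINSA: exact conditional odds ratio 0, 95% interval 0 to 5.29. The size of the risk difference is 7.7 points (Newcombe 95% interval −6.3 to 24.1, baseline minus TINSA).
- 0/26 baseline v 3/26 TINSA: risk difference 3/26 = 11.5 points (−3.4 to 29.0, TINSA minus baseline).
- 0/26 v 0/26: no odds ratio is defined by the data. The Wilson upper limit for 0/26 is 3.84/(26 + 3.84) = 12.9%, so the Newcombe interval is −12.9 to 12.9 points.

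**The case against.** The best counter-argument is that a one-paragraph analysis section in a journal article names a model family, and sparse-data rules are commonly left to an analysis plan, which is not shown. The section does not say maximum likelihood or Wald, and exact and Firth models are themselves forms of logistic regression. That is fair as far as silence goes. But the article does fix the effect measure for all categorical outcomes, and no odds ratio can be had from two phases without events.

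Several stronger readings are tempting, and the document does not support them:

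- **That a zero cell is likely.** This depends on rates the article does not give. At 10% or more, the chance for one outcome is 12.5% or less. The 26 is a requirement and not a cap, and Phases 3 and 4 are limited by time, so actual numbers may differ. If the severity groups were pooled to 52 per arm, the chance would be 57.7%, 13.4% and 0.8% at 2%, 5% and 10%.
- **That falls, pneumonia and pressure injuries each face the problem.** Table 1 pools them into one total, worded as a count. That pooled rate is at least as high as any component's, and logistic regression applies only if the total is analysed as any event, yes or no. The same holds for missed referrals.
- **That the odds ratio never exists with a zero.** With one zero cell it is 0 or infinite, and an exact one-sided bound is available. It is undefined only when both phases are empty.
- **That the plan would return nothing on safety.** Frequencies and percents per group are planned, the economic evaluation compares adverse-event counts, and the monitoring committee reviews increases each fortnight. None of these is a planned between-phase interval, but they are not nothing.
- **That safety is the leading question.** Assessment time is primary and safety is a secondary aim.

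It is also true that the alternative intervals are wide. The sample size limits what can be learnt, and no choice of effect measure changes that.

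**Conclusion.** The point holds in limited form. The stated method and measure suit uncommon binary safety outcomes poorly at about 26 per phase: clearly failed discharge, and also missed referrals and any adverse event if analysed as yes/no. For a single outcome with equal risk in both phases, ordinary logistic regression would give no finite estimate with probability 83%, 46% or 12.5% at assumed risks of 2%, 5% or 10%. It is more likely than not only below about 4.6%. These figures assume exactly 26 patients in each phase, independent patients and separate analysis of each severity group. The consequence is a possibly missing between-phase interval for a secondary aim on which the hypothesis is conditional. The primary analysis of assessment time is not affected.

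**What to change.** In the Quantitative data analysis section, add for binary safety and quality outcomes:

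1. Report the risk difference between phases, within each severity group, with a Newcombe (Wilson score) 95% interval alongside the frequencies and percents.
2. When events are sparse, use Firth-penalised or exact logistic regression in place of ordinary maximum likelihood, so that confounder-adjusted odds ratios remain available. State beforehand what counts as sparse, for example any zero cell.
3. Where neither phase has an event, report the risk difference only. Any finite odds ratio from a penalised fit would then come from the penalty and not from the data.
4. Keep ordinary logistic regression for common outcomes.

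It would help to say in the same place whether adverse events and missed referrals are analysed as counts or as yes/no per patient.

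The cost is one or two sentences and slightly more analysis work; no new data are needed. The drawback is that the Newcombe difference is unadjusted. In a non-randomised pre/post comparison it should stand beside the adjusted analysis and not displace it.

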#### Qualitative data analysis

Open-ended survey responses will be thematically analysed using NVivo Pro software (QSR International). For the semi-closed questions and Likert scales, percentages will be calculated to show how many participants agreed with a pre-defined answer on the survey.

#### Economic evaluation

An economic evaluation will be performed alongside this study. Compared to usual discipline-specific assessment, we seek to determine the change in engagement of hospital resources when the novel TINSA is utilised with patients experiencing stroke. We expect the potential cost-saving to occur at the initial assessment phase of the hospital admission, while other costs incurred during or after the hospital admission will not be affected. The mean cost per patient will be calculated using a decision tree analysis with expected values calculated from observed patient scenarios. To do this, the analysis will take the approach of analysing outcomes in 3 different scopes from the perspective of the health sector (i.e., MHB where the study will take place). Scope 1 will evaluate the initial assessment phase of the hospital admission. Use of resources including AHP time and bed space will be evaluated using AHP assessment times and hospital coded data. Scope 2 will encompass the entire acute hospital admission (inclusive of Scope 1) with multiple measures available from patient medical records and administrative data collection such as occasions of service by AHPs, counts of adverse events (e.g., aspiration pneumonia), and hospital cost per diem (including equipment, consumables, maintenance, and overheads). Scope 3 will be the broadest view, evaluated 3-months after admission to the MHB ASU. In this scope, an extended healthcare perspective will be used, where relevant health costs and healthcare consequences for the patient post-discharge will be considered. For example, counts of adverse events (e.g., number of falls and unplanned readmissions to hospital), quality of life at 3 months measured using the EQ-5D-3L, and increased reliance on informal/formal supports will be compared between groups and (where possible) compared to national medians/means reported by the Australian Clinical Stroke Registry (AuSCR). A one-way sensitivity analysis will be performed to evaluate uncertainty in the cost estimates regarding the TINSA. For example, the costs of AHPs will be examined at the low and high ends of the clinical pay scale for the MHB ASU (e.g., from Health Practitioner Level 3.1 to Level 7.2) [19, 20]; the time of the TINSA assessment will be varied to represent two standard deviations above the mean (i.e., the scenario where costs calculated account for 95% of observations); and length of stay will be varied to represent two standard deviations above/below the mean to capture changes in hospital cost per diem (including equipment, consumables, maintenance, and overheads) for 95% of observations.

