### Study aim

The primary aim of this research is to understand the benefits (or otherwise) of implementing a novel Transdisciplinary Initial Neurological Screening Assessment (TINSA) on the MHB ASU. We hypothesise that compared to the existing discipline-specific allied health stroke assessments, utilising the TINSA will reduce allied health assessment time by at least 20 minutes during the initial occasion of service, without reducing quality of care. Secondary aims are to evaluate use of AHP time across the participant hospital admission, quality of care provided by AHPs in terms of patient safety and compliance to national stroke guidelines, clinical utility of the novel TINSA, economic implications of implementing the novel TINSA, patient and staff satisfaction, staff interprofessional trust, and staff confidence to complete and share transdisciplinary tasks.

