Alongside the TINSA, a competency training package has been developed to foster new skill attainment, standardise assessment administration, and support safe implementation of the novel TINSA. The training package consists of four components: 1) a comprehensive manual, 2) quick reference guide, 3) nine eLearning Modules, and 4) a competency assessment. The nine eLearning Modules and competency assessment are mandatory components of the training package, providing targeted learning on topics which were identified as being beyond the usual scope of practice for a new graduate and/or experienced physiotherapists or occupational therapists. [name] and colleagues describe the development of the TINSA and training package in more detail [12].

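### The economic evaluation aims at the effect of implementing the TINSA, but its stated costs follow the patient episode and so omit the mandatory training; as written it compares running costs only

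*Protocol article*

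**What the plan says.** The Study aim section lists "economic implications of implementing the novel TINSA" among the secondary aims. The Economic evaluation section takes the hospital's perspective and states the unit of costing: "The mean cost per patient will be calculated using a decision tree analysis with expected values calculated from observed patient scenarios".

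It then sets three scopes:

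- **Scope 1:** "Scope 1 will evaluate the initial assessment phase of the hospital admission". The next sentence says "Use of resources including AHP time and bed space will be evaluated" and names two data sources: the recorded assessment times and the hospital's coded data.
- **Scope 2:** the whole acute admission, with Scope 1 inside it.
- **Scope 3:** the patient's costs and consequences after discharge, evaluated 3 months after admission.

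The same section expects the saving to arise at the initial assessment and other costs to be unaffected. It plans a one-way sensitivity analysis and gives pay level, TINSA time and length of stay as examples.

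On training, the section on implementation phases 2 and 4 says: "The nine eLearning Modules and competency assessment are mandatory components of the training package". The Study design section puts competency training and practice in a 1-month transition between Phases 1 and 2.

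**The concern.** Training and competency assessment are hospital-paid staff time, and the hospital's perspective is the one the evaluation adopts. They are needed for the TINSA and not for the usual assessments. Yet they take place between measured phases and belong to no patient's episode, so a mean cost per patient built from observed patient scenarios will not pick them up.

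What is at stake is the reading of the cost result. A cost carried by one side only, if left out, makes that side look cheaper. The plan expects a saving only at the assessment step, so no other expected saving would offset the training. A manager deciding whether to adopt the TINSA needs to know how many patients must be assessed before training has paid for itself, and the evaluation as described would not say.

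**Working it through.** **Step 1. Does any stated cost capture training?**

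| Stated element | What it covers | Training included? |
|---|---|---|
| Scope 1 staff time (Economic evaluation) | Recorded assessment times | No: the primary outcome section limits these to reading the record, assessing and documenting |
| Scope 1 coded data | The patient's admission | No: training belongs to no admission |
| Scope 2 (occasions of service, adverse events, per-diem cost) | The patient's admission | No: overheads sit in a per-day cost that follows length of stay and applies to both groups, so they cannot assign a TINSA-only cost to the TINSA |
| Scope 3 | The patient's costs and consequences after discharge | No |
| Sensitivity analysis examples | Pay level, TINSA time, length of stay | Not named, but the list is illustrative |

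**Step 2. Direction.** Let S be the running saving per patient, H the total training hours and V the number of TINSA patients over which they are spread. In minutes, the net saving per patient is S − 60H/V. Since H is above zero, leaving it out always overstates the net saving. No figure is needed for this.

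**Step 3. Inputs for size.**

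- S = 20 minutes: the hypothesised reduction (Study aim) and the planning difference (Statistical power).
- S = 103 minutes: the pilot result, 145 − 42 (Background).
- H: not given. *Assumption:* 4 to 12 clinicians at 3 to 12 hours each, so 4 × 3 = 12 h up to 12 × 12 = 144 h.
- Wages: not given. *Assumption:* an hour of training costs the same as an hour of assessment saved, so the wage cancels.

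**Step 4. Break-even number of patients, 60H/S.**

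| H | S = 20 min | S = 103 min |
|---|---|---|
| 12 h | 720/20 = 36 | 720/103 = 7 |
| 144 h | 8640/20 = 432 | 8640/103 = 84 |

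**Step 5. Upper-bound allocation to study patients only.** The protocol's sample size is 26 per group. It reproduces from a 20-minute difference, SD 25, two-sided 0.05 and 80% power: 25 by the normal approximation, and 25.5, rounded up to 26, by the t-test. If both TINSA phases reached 26, V = 52. Then 60 × 12/52 = 13.8 minutes and 60 × 144/52 = 166.2 minutes per patient. The gross saving over the same 52 patients would be 52 × 20/60 = 17.3 h or 52 × 103/60 = 89.3 h, against 12 to 144 h of training.

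**The case against.** The strongest reply is that this is silence in a condensed article. The resource lists are worded as examples, nothing says that training is excluded, and a full costing inventory could add it. That stands in part: the sensitivity list is not closed, and a reader should not infer a deliberate exclusion. It does not remove the point, because the article itself states the scopes and the Scope 1 data source, and these follow the patient episode.

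A second reply is that the Economic evaluation section asks what changes when the TINSA is used with patients, which can be read as a running-cost question. For that question, omitting a start-up cost is a legitimate choice of scope. This also stands, but the choice is not stated, and it does not match the aim of costing implementation.

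A third reply is that training lasts beyond the study, so charging all of it to 52 patients is too harsh. That is right. The 26 per group is a power requirement and not the unit's throughput, and after-hours admissions are excluded from the study. The 14 to 166 minutes per patient in Step 5 is therefore an upper-end allocation.

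**Conclusion.** The point holds in a limited form. No stated cost captures the mandatory, TINSA-only training and competency time, so the comparison as described covers running costs. Reported as the economic effect of implementation, it would overstate the saving.

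The direction rests on no assumption. The size rests wholly on assumed hours, headcount and equal wages: break-even at 36 to 432 patients for a 20-minute saving and 7 to 84 for 103 minutes. At the low end with the pilot saving, training is minor. At the high end with the planning difference, it takes several hundred patients to recoup.

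A reader might infer more: that the cost comparison is irretrievably biased, or that training wipes out the saving. The documents support neither. They give no training hours, and the comparison is sound as a running-cost comparison if it is labelled so. The matter concerns one secondary aim and leaves the primary outcome, the sample size and the safety outcomes untouched. It should be corrected, but it does not threaten the trial.

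**What to change.** 1. Log the hours that each clinician spends on the modules and the competency assessment, and the assessor's time.
2. Multiply by wage and enter the result as a separate TINSA implementation cost line alongside Scope 1.
3. Spread it over a stated patient volume or time horizon, such as the unit's annual throughput. Show the allocation to study patients only as an upper bound.
4. Vary the line in the one-way sensitivity analysis already planned, and report the break-even number of patients.
5. Report results with and without the line, and label the version without it as running costs only.

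The cost is a little extra logging and one more cost line; no patient procedure or patient data item changes. The downside is a less favourable saving in the version that includes training.

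### The economic sensitivity analysis is meant to show uncertainty in mean cost, but its two-SD ranges show the spread of individual patients, about √n times too wide for that purpose

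*Protocol article*

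**What the plan says.** All of the rules at issue stand in the protocol article under Economic evaluation.

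- Target: "The mean cost per patient will be calculated using a decision tree analysis with expected values calculated from observed patient scenarios".
- Purpose of the sensitivity analysis: "A one-way sensitivity analysis will be performed to evaluate uncertainty in the cost estimates regarding the TINSA".
- Assessment time: "the time of the TINSA assessment will be varied to represent two standard deviations above the mean", which the article explains as "the scenario where costs calculated account for 95% of observations".
- Length of stay: "length of stay will be varied to represent two standard deviations above/below the mean", again described in terms of 95% of observations.
- A third variation moves staff cost between the low and high ends of the clinical pay scale.

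The three variations are introduced as examples. The section names no confidence interval or resampling method for mean cost. Under Statistical power the article gives the SD and group size used below: "a significance level of 0.05, 80% power and a standard deviation of 25 minutes" and "26 patients per group will be required to detect a 20-minute difference in total assessment time".

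**The concern.** The model produces a mean, so the uncertain inputs are mean assessment time and mean length of stay. The sampling uncertainty of a mean is SD/√n. The article's own gloss shows that its SD is the patient-level one. A cost computed at mean + 2 SD is therefore the cost of an unusually long assessment, not a plausible value of the mean cost.

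At stake is the reading of the economic results, which serve a stated secondary aim. A saving of the size the study is powered to detect could look like a loss when assessment time is moved. In Scope 2, a very wide length-of-stay range could hide a saving measured in minutes. Neither result would say how uncertain the mean cost is.

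**Working it through.** **Inputs.** SD 25 min, 26 per group, smallest important saving 20 min, significance level 0.05, power 80% (Statistical power). The article gives no mean or SD for length of stay, so those values are assumed below and shown as a range.

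**1. Reproduce the planned group size.** The normal approximation, n = 2(1.96 + 0.842)² × 25²/20², gives 24.5, rounded up to 25. The exact two-sample t-test, two-sided, gives 25.52, rounded up to 26. The plan's 26 is reproduced, with power of 80.7%.

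**2. Width for assessment time.**
- Planned shift: 2 × 25 = 50 min.
- Standard error of the mean: 25/√26 = 4.90 min.
- 95% half-width of the mean: 1.96 × 4.90 = 9.6 min, or 10.1 min with t on 25 df.
- Ratio: 50/9.6 = 5.2 or 50/10.1 = 4.95. In general, 2 SD/(2 SD/√n) = √n, which is 5.1 at n = 26 whatever the SD.
- Phases 3 and 4 are limited by time, so n may differ from 26: √15 = 3.9, √20 = 4.5, √52 = 7.2.

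**3. Effect on the conclusion at the plan's own threshold.** Suppose the TINSA saves exactly 20 min and usual-care time is held fixed.
- TINSA time moved up by 2 SD: 20 − 50 = −30 min, a loss.
- TINSA time moved to its upper 95% confidence limit: 20 − 10.1 = 9.9 min still saved.
- For comparison, the 95% interval of the difference between groups has standard error 25√(2/26) = 6.93 min and half-width 13.9 min (t on 50 df). The interval is 20 ± 13.9, or 6.1 to 33.9 min, and excludes zero.

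**4. Length of stay.** The lower bound is mean × (1 − 2·CV), where CV = SD/mean. For an assumed mean of 5 days and n = 26:

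| Assumed CV | mean − 2 SD (days) | mean − 2 SE (days) |
|---|---|---|
| 0.3 | 2.0 | 4.4 |
| 0.5 | 0.0 | 4.0 |
| 0.8 | −3.0 | 3.4 |
| 1.0 | −5.0 | 3.0 |

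The bound is impossible only when the CV exceeds 0.5; the limit based on the standard error stays positive throughout.

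**5. Scope 2.** At an assumed mean of 5 days and CV of 0.5, the range is ± 2 × 2.5 = ± 5 days. If only one group's stay is moved, that stands against a saving of 20 min at the threshold, or 103 min in the pilot (Background). If both groups are moved together, the shift largely cancels in the incremental cost.

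**The case against.** The strongest reply is that this is a deterministic one-way analysis. Its ranges are openly described as covering observations, and they sit beside a pay-scale range that is not a confidence interval either. They can be read as extreme-value scenarios, and moving TINSA time upward only is a stress test against the intervention. The Quantitative data analysis section also promises 95% confidence intervals for differences in continuous outcomes; assessment time and length of stay are both listed outcomes. Scope 1 is evaluated separately and is where the article expects the saving.

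Much of this stands. A reader might infer that the article states wrong error bars; it does not, because it never calls these ranges confidence intervals. A reader might also infer that the study could not tell whether the TINSA saves money. That does not follow: the time saving will have its own interval, and wide bounds in Scope 2 do not erase Scope 1. It is tempting to apply the 25-minute SD to the pilot TINSA mean of 42 minutes and report a move to 92, but no SD is given for the TINSA, so that is not a figure of the plan. That usual-care time is not named for variation, that mean + 2 SD taken one-sided covers 97.7% rather than 95% of a normal variable, and that one-way variation ignores correlation are all minor.

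The mismatch itself is not answered. The article gives the analysis the task of showing uncertainty in the cost estimates, and the ranges do not do that. The promised confidence intervals are for regression-estimated differences, not for a cost from a decision tree. This is a rule the article states, not a detail left to a fuller document.

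**Conclusion.** The concern holds in a limited form: a stated rule does not serve its stated purpose. As a measure of uncertainty in a group mean, the two-SD range is about √n times too wide. That is about 5 at the planned 26 per group, 3.9 at 15 and 7.2 at 52. For assessment time the shift is 50 min against about 10 min, enough to turn the 20-minute minimal important saving into an apparent 30-minute loss. The minutes rest on the planning SD of 25 holding for the TINSA; the ratio does not depend on the SD.

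The length-of-stay consequences are conditional. A negative lower bound needs a CV above 0.5. Swamping the assessment saving in Scope 2 needs a large SD and variation in one group only. The documents neither state nor exclude these conditions, so a reader should not infer that either outcome will occur. The primary outcome is untouched.

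**What to change.** 1. Replace the two-SD ranges for TINSA time and length of stay with the 95% confidence limits of the mean in each assessment group.
2. Report, for each of the three scopes, a bootstrap 95% interval for mean incremental cost, resampling patients within phase and recomputing the decision-tree cost each time. Resampling whole patients also keeps each patient's time, stay and cost together.
3. If the two-SD ranges are kept, label them as extreme-patient scenarios, not as uncertainty in mean cost, and state which group is varied.
4. Leave the pay-scale variation as it is.

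The cost is a few lines of analysis code on patient-level data that the study already collects, and revised wording in one section. No further patients or measurements are needed.
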